### Criteria for discontinuing or modifying allocated interventions

2.5

Key stopping rules for patients are a withdrawal of informed consent or unwillingness to further participate in the trial or any factors affecting the patient's well-being. When participants score above 20 on the PHQ-9; express suicidal ideation (a score MADRS-SR ≥ 4); or write concerning messages in the open text fields, they will be contacted by the research team for a screening. Based on clinical evaluation it will be decided whether a participant should continue the intervention.

### Outcomes

2.6

All outcome questionnaires are self-report scales that participants themselves can fill out via an online secure platform. Assessments are repeated at baseline, 8 weeks, and 12 weeks. An overview of the measurements is giving in Table 3.

**Table 3 t0015:** Questionnaires and measures.

	Screening	Baseline	Weekly in intervention a	8 week post-test	3 M follow up
Eligibility criteria					
Diagnosis of ADHD (self-report) - Date - Venue - Diagnosing physician	x				
Access to pc, smartphone or laptop with Internet connection	x				
Understands Norwegian	x				
Current stable use of ADHD medication (self-report) - Yes - No - Type	x				
Ongoing substance abuse (self-report)	x				
Self-reported severe mental illness such as borderline or antisocial personality disorder, bipolar disorder and/or mental retardation	x				
Currently receiving psychological treatment for ADHD	x				
Availability for the next 4 weeks	x				
MADRS-SR (item 10; suicidality)	x	x		x	x
Demographic variables questionnaire - Gender - Age - Educational level - Occupational status - Personal contact information (email, telephone number) - Postal code	x	x			
ASRS		x	x	x	x
AAQol		x		x	x
PHQ-9		x		x	x
GAD-7		x		x	x
PSS		x		x	x
Changes in medication and engagement in other therapeutic interventions questionnaire		x		x	x
Self-report adverse events				x	x

Usability measures					
Use, benefit and understanding of the modules components (questionnaire specifically design, open questions)			x		
CEQ		x		x	x

Participant-generated data					
User login Completed modules Completed questionnaires Completed homework Completed assignments Time spent on reading material Time spent on module/exercise Clicks			x	x	x

Content evaluation					
Participant feedback within the program			x		

a These measures will only be filled out by the intervention group. AAQOL-29: Adult ADHD Quality of Life Scale. ASRS: the adult ADHD self-rating scale. CEQ: credibility and expectancy scale. MADRS: Montgomery And Åsberg Depression Rating Scale. MADRS SR: Montgomery And Åsberg Depression Rating Scale Suicide Rating. PHQ-9: patient health questionnaire 9. PSS: perceived stress scale.

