### Informed consent and withdrawal from the study

2.3

Participants who are eligible to participate in the study, as assessed by a pre-screening questionnaire and a follow-up telephone interview, will have to sign a consent (see questionnaires and participant timeline section). The consent will be signed digitally in a secure portal with BankID (level 4 protection). Participants can end their participation at any time and for any reason. In addition, should the condition of a participant deteriorate, supervising clinicians may choose to end the participation prematurely and direct the participant to official health care services.

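### Adverse events are scheduled to be asked about only at 8 weeks and 3 months, so people whose participation ends entirely before week 8 may go unasked

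*Protocol article*

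**What the plan says.** Table 3 (section 2.6) has a single row for harms, "Self-report adverse events". It is marked under the 8-week post-test and the 3-month follow-up, and not under the weekly column. Section 2.6 gives the general timetable: "Assessments are repeated at baseline, 8 weeks, and 12 weeks". Footnote a to Table 3 says of the weekly measures: "These measures will only be filled out by the intervention group".

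The document expects some people to leave before week 8. Section 2.3 states "Participants can end their participation at any time and for any reason", and adds that "should the condition of a participant deteriorate, supervising clinicians may choose to end the participation prematurely". Section 2.5 names three signals: a PHQ-9 score above 20, a MADRS suicidality score of 4 or more, and worrying free-text messages. For these, "they will be contacted by the research team for a screening", and "Based on clinical evaluation it will be decided whether a participant should continue the intervention". Section 2.4.2 lets control participants contact the team, or be contacted, if their symptoms rise. None of these places mentions an adverse-event record.

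Step 2 of section 2.7.1 refuses platform access to people who do not meet the criteria, and says that exclusion from the study is handled the same way. Section 2.6 places the outcome questionnaires on that online platform.

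**The concern.** The adverse-event question is tied to two fixed assessments, but ending participation for deterioration can happen at any time. Someone taken out of the study in week 3 because they are getting worse has, on the published schedule, no point at which the question is put to them, and may no longer have access to the platform where it sits. That person is among those whose harms most need recording.

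The programme is self-guided, so the team does not see participants routinely between assessments. If early leavers are not asked, the count of people with an event is too low. If they also have more events than those assessed, the rate among those assessed is too low as well.

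**Working it through.** **1. Who is exposed.** Setting the sections side by side gives four groups.

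- *Stops the intervention but stays in the study.* Section 2.5 decides on continuing the intervention, not on assessment. Section 2.7.1 sends reminders for both later assessments and compensates each completed one. Section 2.12 uses all data whatever the compliance. These people can still answer the form.
- *Triggers a contact through PHQ-9 or MADRS.* Neither scale has a weekly mark in Table 3. After baseline they fall at the same two assessments as the adverse-event form, so such a trigger coincides with the form.
- *Raises concern before week 8 by another route.* This means free text or, in the control arm, direct contact. The weekly open questions exist only in the intervention arm, so detection by this route can differ between arms.
- *Participation ends entirely before week 8* (section 2.3, by own choice or by clinicians). No adverse-event question is scheduled for them. This is the exposed group.

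**2. How large the group could be.** The document does not forecast early exits for harm. The only related figure is the attrition allowance in section 2.8: 45 × 1.3 = 58.5, rounded up to 59 per arm, which reproduces the plan's figure. The allowance is therefore 59 − 45 = 14 per arm, 14/59 = 23.7%, or 28 of 118. If 30% were actually lost, it would be 0.30 × 118 = 35.4, about 35 people. Both cover attrition for any reason, so they probably overstate exits for harm.

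**3. What could be missed.** Let d be the share never asked at either assessment, RR their event risk relative to those assessed, and p the risk in those assessed. Then:

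- share of people with an event who are captured = (1 − d) / [(1 − d) + d × RR]
- true rate = p × [(1 − d) + d × RR]; rate among those assessed = p

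RR and p = 10% are assumptions; the document gives neither.

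| RR | Captured, d = 23.7% | True rate, d = 23.7% | Captured, d = 30% | True rate, d = 30% |
|---|---|---|---|---|
| 1 | 76% | 10.0% | 70% | 10.0% |
| 2 | 62% | 12.4% | 54% | 13.0% |
| 3 | 52% | 14.7% | 44% | 16.0% |
| 5 | 39% | 19.5% | 32% | 22.0% |

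Worked line: d = 0.237 and RR = 3 give 0.763 / (0.763 + 0.237 × 3) = 0.763 / 1.474 = 0.52, and a true rate of 0.10 × 1.474 = 14.7%, against 10% among those assessed.

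The first row matters: with equal risk the rate among those assessed is right and only the count is low. All rows assume that no one in the allowance is asked at either assessment and that no other record exists, so they show the worst case for each RR.

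**The case against.** The best case on the other side is that Table 3 is a schedule of questionnaires which participants fill in themselves. A staff log of unscheduled events would not normally be a row in it, and a condensed article commonly leaves such a log to the full protocol. Sections 2.3, 2.4.2 and 2.5 show that deterioration can come to the team's notice, and nothing says that what is learned there goes unrecorded. The exclusion sentence in section 2.7.1 stands in the screening step and may not have been written with later exits in mind. The document also defines no adverse-event rate, denominator or between-arm comparison of harms.

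Most of this stands, and it limits the point. A reader might infer that events in early leavers are never recorded, that harm is therefore understated, or that the comparison between arms is biased. The document supports none of these: the first rests on silence about other records, the second needs leavers to have more events, and the third concerns an analysis that is not described. Nor does it support the idea that people are stopped before week 8 on scheduled PHQ-9 or MADRS scores, because after baseline those scores arrive together with the form.

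What remains does not rest on silence alone. The document fixes where its only adverse-event instrument is used, allows participation to end before that, and, read naturally, removes platform access on exclusion.

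**Conclusion.** The point holds in a limited form. People whose participation ends entirely before week 8, including those ended for deterioration, are not scheduled to be asked about adverse events, so harms may be under-counted. People who stop only the intervention are not affected.

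The size is unknown. If the whole attrition allowance went unasked, between 76% (equal risk) and 39% (five times the risk) of people with an event would be captured, or 70% to 32% if 30% were lost. These ranges rest on assumed relative risks and on an allowance that covers every reason for leaving. Bias in the rate, as opposed to a low count, requires early leavers to have more events than those assessed. That is plausible, since deterioration is itself a ground for ending participation, but the document gives no figure for it. This is a cheap improvement to the harms evidence and leaves the efficacy analysis untouched.

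**What to change.** - In Table 3, add a collection point for early end of participation, in both arms. Use the existing adverse-event questions plus the reason for ending, where the participant agrees to answer.
- Make clear in section 2.7.1 how the questions reach someone whose platform access has ended.
- Report adverse events by arm with all randomised participants as the denominator, and state how many in each arm were never asked.
- List events learned through section 2.5 contacts or control-arm contacts separately from the scheduled self-report. Pooling them would add detection that differs by arm, because the weekly open-text fields exist only in the intervention arm.
- Recruitment is finished and the first group has completed its assessments (Trial status), so for exits that have already happened use the existing discontinuation records.

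No stopping or contact rule changes. The cost is slightly more recording, a possibly higher reported rate, and uneven capture between earlier and later participants, which the report should state. People who leave without any contact will still be missed, which is why the number never asked has to be given.

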#### Primary outcome measure

2.6.1

#### Secondary outcome measures

2.6.2

##### Adult ADHD Quality of Life Measure (AAQol)

2.6.2.1

The AAQoL has 29 items designed to assess health related quality of life during the past two weeks among adults with ADHD (Gjervan and Nordahl, 2010). Each item is rated by participants on a five-point Likert scale. The AAQoL yields a total score (based on all 29 items) and four subscale scores: Life Productivity, Psychological Health, Life Outlook, and Relationships. Internal consistency is acceptable, with Cronbach's alpha >0.70 for all subscales.

##### The perceived stress scale (PSS)

2.6.2.2

The Perceived Stress Scale (PSS) is a widely used psychological instrument for measuring stress (Cohen et al., 1994). Items were designed to measure stress and how uncontrollable respondents find their lives during the week (Cohen et al., 1983). The PSS version used in this study has 10 items with response alternatives 0 (never) to 4 (very often) and Cronbach's alpha has been reported to be 0.89 (Roberti et al., 2011).

##### The Patient Health Questionnaire-9 (PHQ-9)

2.6.2.3

The Patient Health Questionnaire-9 (PHQ-9: (Kroenke et al., 2001)) is a self-report tool used to assess the presence and severity of depressive symptoms. Reliability and validity of the tool have indicated that it has sound psychometric properties. Internal consistency of the PHQ-9 has been shown to be high. A study involving two different populations in Norway produced Cronbach alphas of 0.86 and 0.88 (Wisting et al., 2021).

#### Usage, user satisfaction and engagement

2.6.3

##### Usage

2.6.3.1

During the intervention, the following measures of activity and compliance will be measured; number of logins; number of finished exercises; total time spent on modules and exercises; and finally, how many pages each participant finished.

User satisfaction is measured by four open-end questions at the end of each of the modules:1.Were there parts of the module that you experienced as helpful and/or supportive?2.Were there parts of the module that you experienced as complicated and/or unhelpful?3.Would you recommend this module to a friend or a family member with similar difficulties as yourself?4.How useful did you find this module? 1–10

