### Objectives

1.2

The primary objective of this study is to evaluate the effects of a self-guided Internet-delivered psychological intervention on i) symptoms of inattention and quality of life in adults with ADHD, and ii) symptoms of hyperactivity, stress and depression. These effects will be compared with results obtained in a group of adults with ADHD randomized to a psychoeducation control condition. The secondary objective of the study is to explore user satisfaction with and adherence to the intervention.

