#### Procedure

2.7.1

*Step 1*. *Online anonymous survey*. The survey will take place in an open version of an online platform with no BankID login. The following questions are asked in step 1:

1. Are you 18 years or older?

2. Do you have a diagnosis of ADHD?

3. Do you have time to actively participate in the study over the next 12 weeks?

4. Do you have access to a computer or smartphone with Internet?

5. Are you able to read and write Norwegian?

When not meeting inclusion criteria, participants are rejected access to the intervention. To meet inclusion criteria, the participant will have to answer yes on all the five questions above.

*Step 2*: *Telephone screening*. Eligible participants will be asked to schedule an appointment for screening by telephone with a member of the research team. During the screening they will be asked about the following:

1. Age when diagnosed with ADHD.

2. Venue where the ADHD diagnosis was given.

3. Current symptoms of ADHD.

4. Day-to day functioning (work, school and social).

5. Suicidality (Item 10 MADRS).

6. Symptoms of depression.

7. Symptoms of psychosis.

8. Symptoms of bipolar disorder.

9. Substance use.

10. Current psychological treatment or other psychological treatment needs.

11. Motivation.

12. Name.

13. Email address.

14. National identity number.

When not meeting inclusion criteria, participants are rejected access to the platform. If necessary, they will be referred to other appropriate sources of support. The same procedure will be followed if exclusion from the study is needed.

*Step 3*: Signing consent. Participants who are eligible to participate in the study will have to sign a consent to participate in the study. The consent is digitally signed in a secure online portal with BankID.

*Step 4*: *Randomization*. Participants who are eligible for the study will be randomized with sealed envelopes and assigned to one of two groups: the internet-delivered intervention or (psychoeducation) control group.

*Step 5*: *Pre-intervention measurements*. After signing the informed consent form, participants fill out a second set of questionnaires that form the pre-intervention measurements. The questionnaires are all distributed online in a level 4 safe and secure environment (BankID). All questionnaires are shown in Table 3. As a compensation for the time used on completing the questionnaires the participants will receive a 200 NOK gift card for each completed assessments (pre, post, 3 M FU).

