### Sample size

2.8

Power calculations are informed by the feasibility study of MyADHD (Nordby et al., 2021) providing an effect corresponding to Cohens d: 0.70 on the primary outcome measure ASRS. The minimum sample size for each group (alpha set at 0.05, power at 0.95) is identified to be 45, but at least 30% more will be recruited to hedge against expected attrition (*n* = 59). The minimum total sample size will be *N* = 118. It seems realistic to recruit this in a group with an estimated prevalence of 2–3% (Franke et al., 2018).

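### User satisfaction is asked only at the end of each module, so the ratings depend on finishing modules and probably flatter the later ones

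*Protocol article*

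**What the plan says.** Section 1.2 (Objectives) states: "The secondary objective of the study is to explore user satisfaction with and adherence to the intervention". Satisfaction is thus one of two parts of that objective.

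Section 2.6.3.1 (Usage) names the measure and its timing: "User satisfaction is measured by four open-end questions at the end of each of the modules". The four questions cover what helped, what was complicated or unhelpful, whether the person would recommend the module, and one numeric item: "How useful did you find this module? 1–10".

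Table 3 in section 2.6 has a row that fits this questionnaire, "Use, benefit and understanding of the modules components (questionnaire specifically design, open questions". It is marked only in the weekly intervention column, whose footnote says: "These measures will only be filled out by the intervention group". The 8-week and 3-month columns hold no measure labelled satisfaction and no question on why someone stopped.

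Two neighbouring measures exist. Table 3 lists "Participant feedback within the program" in the weekly column, and it marks the CEQ at baseline, 8 weeks and 3 months.

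**The concern.** A question placed at the end of a module is answered by people who reach that end. In a self-guided programme, those who leave a module partway may well do so because it did not suit them, and theirs is the opinion that this placement misses. The question on what was complicated or unhelpful has most to offer in the module where a person gave up, and that is the one module the person does not rate.

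The plan itself expects losses. It lists attrition among the usage outcomes of interest (section 2.6.3.3) and sends reminders for unfinished modules (sections 2.4.1 and 2.7.1). For the clinical outcomes, section 2.12 includes all participants' data whatever their compliance. Satisfaction, by contrast, is collected only where there was compliance. A reader of the results could take the ratings of finishers as the view of everyone offered the programme.

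**Working it through.** **Step 1: who can answer.** Seven modules are released weekly (section 2.4.1), each followed by the four questions.

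| Participant in the intervention arm | Module ratings given |
|---|---|
| Finishes all seven modules | Modules 1 to 7 |
| Stops during module k+1, with k from 1 to 6 | Modules 1 to k; none for module k+1, where the person stopped |
| Finishes no module | None |

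The group rating module 7 is therefore a self-selected part of the group rating module 1. Section 2.4.1 also calls the six themed modules optional, while Table 1 heads the modules as obligatory. If they are optional, raters also select themselves module by module.

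**Step 2: what else is collected.**
- CEQ (section 2.6.3.2): asked at 8 weeks and 3 months whatever was completed, but it measures credibility and expectancy of improvement.
- Feedback within the program (Table 3): no completion condition is stated, but it is marked weekly only, is given inside the program, and is not named as the satisfaction measure.
- Platform records (section 2.6.3.1): these cover people who stop and show when they stopped, but not why or how satisfied they were.

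None of these is a satisfaction rating from people who stopped.

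**Step 3: size, by assumption.** The document gives no satisfaction figure to reproduce and no rate of stopping the modules. Let d be the share of the arm that stops before the end of the last module. Let F be the mean usefulness rating of those who finish it, and S the mean that the others would have given.

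- Mean over the whole arm = (1 − d) × F + d × S
- Mean observed = F
- Excess = F − [(1 − d) × F + d × S] = d × (F − S)

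With 59 in the intervention arm (section 2.8), and F − S assumed to be 1 to 3 points:

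| d (assumed) | Last-module raters, 59 × (1 − d) | Excess, gap of 1 point | Excess, gap of 3 points |
|---|---|---|---|
| 0.10 | 53 | 0.1 | 0.3 |
| 0.30 | 41 | 0.3 | 0.9 |
| 0.50 | 30 | 0.5 | 1.5 |

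The same formula holds for each earlier module with its own d. Fewer people have stopped by then, so for a given gap the excess is smaller. If those who stop are as satisfied as those who stay, the excess is zero.

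**Step 4: can d be taken from the sample size section?** Section 2.8 says "at least 30% more will be recruited to hedge against expected attrition": 45 × 1.30 = 58.5, rounded to 59. Recruiting 59 to keep 45 allows a loss of 14/59 = 24%. That allowance concerns loss to the study, not stopping the modules, so it does not fix d. It only shows that losses within the assumed range are not far-fetched.

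**The case against.** A reader might infer that the views of people who stop are never collected. The documents do not support that. Someone who stops after module 3 has already rated modules 1 to 3, including what was unhelpful. Feedback within the program has no stated completion condition, and the CEQ reaches people who left the modules but still answer assessments.

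A reader might also infer that the whole secondary objective rests on finishers. It does not. Adherence comes from logins, pages, time and attrition, which cover people who stop.

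A third temptation is to quote one figure for an inflated overall satisfaction score. The plan defines no overall score, the objective is exploratory, and such a figure would give no weight to anyone who stopped, although many of them will have rated some modules. Borrowing the 30% allowance would add a further mismatch, because people lost to the study would often miss the 8-week assessment too.

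It can also be said that rating a module after using it is ordinary practice, that the article is condensed, and that the full protocol may contain an exit question. The first of these is fair, and nothing is wrong with keeping the module-end questions. On the second and third, the article does fix the timing of the named measure, and Table 3, which sets out the questionnaires, marks nothing for satisfaction at the later assessments. The possibility of an exit question elsewhere remains open.

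Finally, the section headed Trial status says that recruitment is finished, a first group has completed intervention and assessments, and a second is finishing. This limits what new questions can still reach, but not what can be reported.

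**Conclusion.** The point holds for the satisfaction part of the secondary objective. The only named satisfaction measure is conditional on finishing a module. The module in which a person stops goes unrated by that person, people who finish none contribute nothing, and later-module ratings come from those who persisted. The direction of bias is upward if those who stop are less satisfied, which is plausible but not shown in the document.

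The size cannot be derived from the document. Under the stated assumptions (10% to 50% stopping, a gap of 1 to 3 points), a last-module usefulness mean is too high by about 0.1 to 1.5 points. The other measures are partial substitutes only. Adherence and the clinical outcomes are untouched. This is a cheap, worthwhile improvement rather than a threat to the trial's main conclusions.

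**What to change.** Keep the module-end questions and make two changes.

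1. Add three items to the 8-week post-test, worded for the programme as a whole, for all intervention-arm participants whatever they completed: the 1–10 usefulness rating, the recommendation item, and one question on the reason for stopping. For participants already past 8 weeks, place them at the 3-month follow-up if that is still pending. Both assessments are already scheduled and carry reminders (section 2.7.1, Step 6), and both are compensated: "the participants will receive a 200 NOK gift card for each completed assessments".
2. Report each module's ratings beside the numbers offered, started and finished, and state that the ratings come from people who finished that module.

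The cost is three questions in an existing online assessment, with slightly more burden. People who also skip these assessments stay unobserved, and participants whose assessments are complete cannot be reached by the new items. The second change costs almost nothing and, since usage is already recorded, can be made for the whole arm whatever the stage of the trial.
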